Each exercise session will be monitored via a GENEActiv device (GENEActiv, Activinsights, Cambridge, UK) worn on the wrist [77] to determine compliance. Compliance records will be cross-checked with an activity diary where participants record the date, time, duration, difficulty and total revolutions of each exercise session along with average heart rate during the last 10 minutes of exercise. Sampling at 30 Hz, the GENEActiv is capable of recording PA for up to 3 weeks. At the midway point a newly initialised and charged GENEActiv device will be sent to the participant by standard mail. During the final week of the intervention exercise intensity compliance will be checked by heart rate recordings on the Actiheart™ monitor. Adherence to the intervention will be maintained with regular weekly telephone calls and emails. No dietary constraints will be imposed: participants in both groups will be free to consume food and fluid ad libitum throughout.

### Outcome measures

#### Body composition, resting metabolic rate and aerobic capacity

To determine body composition, DEXA scans will be analysed for total and regional (trunk, legs, arms) fat mass, fat free mass, bone mineral content and fat percentage, following the guidelines described in the user manual (Hologic, Bedford, UK). Fasting respiratory exchange ratio (RER) will also be calculated during the resting metabolic rate (kcal day^−1^) measurement. Aerobic capacity will be measured at the point of volitional exhaustion during the incremental arm-crank test. A number of criteria (participants must meet two of these) will be applied to determine whether this endpoint is reflective of a valid V̇O_2_ peak value. These were: (1) a peak RER value ≥1.1, (2) a peak heart rate of 95 % or more of the age-predicted maximum (200 b min^−1^ minus chronological age) and an increase in V̇O_2_ ≤ 2 ml kg^−1^ min^−1^ in response to an increase workload [70]. Moreover, peak workload (W) will be measured at volitional exhaustion.

#### Blood measurements

The metabolic and cardiovascular health, along with immune function variables measured are shown in Table 1. Besides the haematological profile which is measured immediately during the main trial day, these variables will be quantified during a batch analysis once the final participant has completed the study. In order to simplify data analysis and facilitate the interpretation of a complex data set [78, 79], serial measurements of glucose and insulin responses to the OGTT at baseline and follow-up will be converted into simple summary statistics [80], such as incremental area under the curve (iAUC) [81] and insulin sensitivity index (ISI_Matsuda_) [82]. The Homeostasis Model Assessment (HOMA) calculator, incorporating the updated HOMA-2 model [83], will be used to derive fasting estimates of pancreatic β-cell function, insulin resistance and sensitivity.

**Table 1 Tab1:** Metabolic health, cardiovascular disease risk and immune function variables

Haematological profile	Analytical techniques
Red blood cell, white blood cell, neutrophil, lymphocyte, monocyte and platelet counts, haemoglobin concentrations, haematocrit and haematic indices	Automated haematology system (SF-300, Sysmex Ltd., Milton Keynes, UK)
Biochemical variables	Analytical techniques
Triglycerides, total cholesterol, NEFA, HDL-C, LDL-C, glucose	Automated analyser (Randox RX Daytona, Randox Laboratories, Co. Antrim, UK), in accordance with manufacturer’s instructions using commercially available immunoassays (Randox Laboratories, Co. Antrim, UK).
Insulin	ELISA (Mercodia AB, Uppsala, Sweden)
Adipokines	Analytical techniques
Leptin and adiponectin	ELISA (Quantikine HS, R&D Systems Inc., Abingdon, UK)
Inflammation	Analytical techniques
IL-6	ELISA (Quantikine HS, R&D Systems Inc., Abingdon, UK)
CRP	Automated analyser (Randox RX Daytona, Randox Laboratories, Co. Antrim, UK),
Immune function	Analytical techniques
T cell anti-viral IFN-γ production	Human IFN-γ ELISpot^BASIC^ (Mabtech, Nacka Strand, Sweden)

*CRP* C-reactive protein, *ELISA* enzyme-linked immunosorbent assay, *ELISpot* enzyme-linked immunospot, *HDL-C* high-density lipoprotein cholesterol, *IFN-γ* interferon gamma, *IL-6* interleukin-6, *LDL-C* low-density lipoprotein cholesterol, *NEFA* non-esterified fatty acid

#### Adipose tissue gene expression

The aqueous phase of stored adipose tissue samples will be isolated and total ribonucleic acid (RNA) extracted using the standard protocol supplied with RNeasy mini columns (Qiagen, Crawley, UK). Approximately 2 μg of total RNA will be reverse transcribed using a high-capacity complementary deoxyribonucleic acid (cDNA) reverse transcript kit (Applied Biosystem, Warrington, UK). Pre-designed primers and probes will be obtained from Applied Biosystems for each gene tested. Real-time polymerase chain reaction (PCR) will be performed using a StepOne™ (Applied Biosystems, Warrington, UK).

#### Measures of health and wellbeing

Quality of life and health status will be measured using the SF-36 [84] and EQ-5D-5 L [85] self-report questionnaires, with certain questions adapted for wheelchair propulsion instead of ambulation. Compared with four other instruments used to measure health-related quality of life in persons with SCI, Leduc and Lepage [86] reported better validity of the SF-36 with regard to quantifying the health status of participants. Original responses will be transformed into recorded values (taking into account items which were negatively scored) and specific questions will be averaged to return a value for general health using the RAND 36-Item Health Survey 1.0 scoring method. This value will range from 0 to 100, with 100 representing the best health possible. The EQ-5D-5 L was developed by the EuroQol group and is applicable to a wide range of health conditions, including individuals with SCI [87].

Shoulder pain will be assessed using the WUSPI [88]. The performance-corrected WUSPI score (PC-WUSPI) will be used as it accommodates participants who are unable to undertake certain functions (i.e. item 13: driving?). This correction multiplies the average response for all items by the number of questions attempted, with higher values indicating a greater degree of perceived shoulder pain. The FSS will be administered to measure the severity of fatigue and its effects on certain behaviours. The FSS was initially developed to be used in multiple sclerosis patients [89], but has also been shown to have acceptable test-retest reliability and validity in 48 community living individuals with SCI [90]. Self-efficacy will be assessed using the SCI ESES [91], which was developed specifically to cover issues associated with this unique population.

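### The formula printed for the performance-corrected shoulder pain score (PC-WUSPI) does not correct for items a participant cannot do, so it does not serve its stated purpose

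*Protocol article*

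**What the plan says.** The protocol article covers this in Outcome measures, under Measures of health and wellbeing. It gives three things in sequence.

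- **Purpose.** "The performance-corrected WUSPI score (PC-WUSPI) will be used as it accommodates participants who are unable to undertake certain functions". The example given is "i.e. item 13: driving".
- **Formula.** "This correction multiplies the average response for all items by the number of questions attempted".
- **Direction.** "with higher values indicating a greater degree of perceived shoulder pain", so a lower score is read as less pain.

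The article gives no other scoring rule for this questionnaire and does not state how many items it has. The questionnaire is completed at both laboratory visits, since the main trial day procedures are the same at baseline and follow-up. The Statistical analysis section applies standardised effect sizes and magnitude-based inferences to all variables, so this score will be among those interpreted.

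**The concern.** A performance correction is meant to make scores comparable between someone who can do every listed task and someone who cannot. It therefore has to raise the raw total when items are missing. The printed formula cannot do so: it gives the raw total or something smaller.

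If the sentence is coded as written, a participant who skips items and reports some pain on the rest gets a score that depends on how many items were attempted as well as on how much they hurt. Two consequences follow for the change from baseline:

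- If the same items are skipped at both visits, the change is shrunk.
- If the number attempted differs between visits, part of the apparent change reflects that difference and not pain.

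The planned groups are 16 and 8 participants, so a few such scores could move a group mean.

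**Working it through.** **Inputs**

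- Purpose and formula: Measures of health and wellbeing, as quoted above.
- Total number of items, K: not stated. An item 13 is mentioned, so K is at least 13. K = 13 to 15 is an assumption used to show the range.
- k = number of items attempted; S = sum of the responses given.
- The article gives no numerical figure to reproduce. The check is algebraic.

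**Reading A: average over the attempted items**

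(S/k) × k = S. This is the raw total, whatever the responses are.

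**Reading B: average over all items, skipped ones counted as zero**

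(S/K) × k = S × k/K. This is below S whenever k < K and S > 0.

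**Comparator: prorated score**

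(S/k) × K. If the mean response per attempted item is m, then S = m × k and the prorated score is m × K, which does not depend on k.

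**Ratios to the prorated score**

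- Reading A: S ÷ (S × K/k) = k/K.
- Reading B: (S × k/K) ÷ (S × K/k) = (k/K)².

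These measure a shortfall only on the assumption that the skipped items would have scored, on average, the same as the attempted ones.

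| Items skipped | A, K = 13 | A, K = 15 | B, K = 13 | B, K = 15 |
|---|---|---|---|---|
| 0 | 1.000 | 1.000 | 1.000 | 1.000 |
| 1 | 12/13 = 0.923 | 14/15 = 0.933 | 0.852 | 0.871 |
| 2 | 11/13 = 0.846 | 13/15 = 0.867 | 0.716 | 0.751 |
| 3 | 10/13 = 0.769 | 12/15 = 0.800 | 0.592 | 0.640 |

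**Worked case.** Assume K = 15, two items skipped (k = 13) and a mean response of 4 on the attempted items. Then S = 52.

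- Reading A: (52/13) × 13 = 52.
- Reading B: (52/15) × 13 = 45.1.
- Prorated: (52/13) × 15 = 60.

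**Change scores.** If the same items are skipped at both visits, the change is multiplied by k/K on Reading A and by (k/K)² on Reading B, relative to the change in the prorated score.

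**What prorating does not repair.** Assume K = 15, with fourteen items scored 2 and one scored 8, a total of 14 × 2 + 8 = 36. If the participant stops doing the painful task and nothing else changes, the raw total becomes 28 and the prorated score (28/14) × 15 = 30. The spurious fall is 8 points on the raw total and 6 points after prorating.

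**The case against.** The strongest reply is that this is a slip of wording. The article names an existing corrected score, cites the instrument and states the purpose correctly, and only the clause giving the formula goes wrong. Whoever scores the data may follow the published rule, which cannot be checked from this document. That stands as a limit on the claim: the trial's scores are wrong only if the sentence is applied as written. It does not remove the point, because this sentence is the only scoring rule given and anyone working from it would apply no correction.

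A reader might also infer more than the article supports, in four ways.

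- **That the score always equals the uncorrected total, or always loses 1/K per skipped item.** Both hold only on Reading A. On Reading B the score is lower still.
- **That affected participants certainly score falsely low pain.** The percentages assume that skipped items would have hurt as much as attempted ones. Nothing in the article establishes this, and if a skipped item would have scored zero, the raw total is not low.
- **That correcting the formula removes false improvement when a painful task is abandoned.** It does so only in part: in the example above, 6 of the 8 points remain.
- **That this is the trial's detector of upper-limb harm from arm-cranking.** It is the shoulder-specific questionnaire in a trial of arm exercise, but the article gives it no safety role. It is one of five questionnaires in a wellbeing category.

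The practical effect may also be small. People reporting active upper-limb musculoskeletal complaints are excluded, so baseline scores may be low, and the article does not say how many participants would skip an item. The rule is the same in both groups.

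**Conclusion.** The point holds as a minor one. As worded, the formula contradicts the purpose given in the sentence before it, on either reading of the average. This is settled by algebra and needs no outside source.

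The size is conditional. For a participant who skips at least one item and reports some pain, with K assumed to be 13 to 15 and skipped items assumed to resemble attempted ones:

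- Reading A is about 7–8% low for one skipped item and 13–15% low for two.
- Reading B is about 13–15% low for one skipped item and 25–28% low for two.

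Participants who answer every item get the same score under all versions. Fasting insulin, on which the sample size rests, is untouched. How far the trial's shoulder pain results would be affected cannot be estimated from the article, because it does not give the frequency of skipped items or confirm that the sentence will be coded literally.

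**What to change.** Replace the formula with: PC-WUSPI = (sum of responses to attempted items ÷ number of items attempted) × total number of items in the questionnaire. State that total, and apply the rule identically at baseline and follow-up.

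It would also help to report how many items each participant attempted at each visit, since prorating cannot fully offset the selective dropping of an unusually painful task.

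The cost is one sentence and one line of scoring code. No new data are needed as long as the item-level responses have been kept: the Trial status section reports 21 of 24 participants recruited at 2 February 2016, and scores already computed can be recalculated from those responses. If the intended scoring already follows this rule, only the sentence needs correcting.

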### Physical activity energy expenditure

Daily physical activity energy expenditure will be estimated before and during the final week of the INT/CON period using an Actiheart™ monitor. Entering heart rate and corresponding J min^−1^ kg^−1^ (derived from indirect calorimetry) data measured throughout the trial day (at rest and during a range of submaximal/maximal exercise intensities) into the manufacturer’s software permits the individual calibration of this device. This method has been previously validated for use in wheelchair users [71]. Raw acceleration signals (expressed as g min^−1^) will also be recorded at baseline and follow-up using a GENEActiv device worn on the wrist [77]. The number of days required to assess habitual PA using wearable devices has been discussed at length [92]. The consensus was that monitoring for 3–4 days is required to achieve 80 % reliability in activity counts. In our work we decided to use an inclusion criteria of 4 days or more (providing one of these days was a weekend day). This criteria also ensures that we capture more PA behavioural information than the physical activity recall assessment for people with a spinal cord injury (PARA-SCI: 3-day recall telephone interview) which has been widely used to quantify free-living PA in wheelchair users [53, 93]. A valid day will require at least 80 % of data for that 24-h period. Data will also be expressed as minutes spent in different intensities of activities on the basis of metabolic equivalents (METs): sedentary <1.5 METs, light- 1.5–2.9 METs, moderate- 3.0–6.0 METs, and vigorous-intensity activity >6.0 METs.

### Energy intake

Participants will be asked to keep a detailed record of their food and fluid intake for a ‘typical’ 7 days. Previous work has demonstrated variation between weekday and weekend energy intake [94]; therefore, 7 days is a suitable period to allow accurate representation of habitual energy intake. Each participant will receive a set of weighing scales (PL11B Digital Scale, Smart Weigh, Chestnut Ridge, NY, USA) to accurately weigh and record foodstuffs, which negates any potential errors in the estimation of food weight [95]. Martin et al., [96] have shown that weighed food records are a more valid measure of energy intake than dietary recall methods. Diet records will subsequently be analysed using Nutritics software (Nutritics Ltd., Dublin, Ireland), to estimate energy intake and macro-nutrient composition.

### Statistical analysis

Changes in key outcome variables within and between trials will be analysed with two-way (group [INT, CON] × day [baseline, follow-up]) and three-way (group [INT, CON] × day [baseline, follow-up × time]) mixed-model analysis of variance (ANOVA). Where significant interactions are observed, multiple *t* tests will determine the location of variance both between treatments at each time point and between time points within each treatment relative to baseline. Both methods will be subjected to a Holm-Bonferroni stepwise adjustment [97]. Standardised effect sizes (Cohen’s *d*) will also be calculated for all variables. Based upon the magnitude of correlation between trials, thresholds of >0.2 (small), >0.5 (moderate) and >0.8 (large) have been suggested [98]. This provides an interpretation of the size of the effects in our outcome measures when using a parallel-group’s study design. Magnitude-based inferences will also be calculated to examine the impact of exercise on all variables of interest.

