After baseline laboratory testing and habitual free-living monitoring, the first nine participants will be randomly allocated to the experimental group (INT) or the CON group using a block randomisation plan (fixed block size of nine; allocation ratio of 2:1; no stratification). Randomisation will be performed by an independent researcher using a concealed list generated with a web-based platform (www.randomization.com). Within a highly heterogeneous population such as individuals with SCI, we decided to use minimisation [67] to ensure balance between the two groups for baseline characteristics (age, body mass, level of spinal cord lesion and physical activity level). Subsequent participants who enrol on the trial will, therefore, be allocated to either the INT group or the CON group in order to balance the groups in these variables of interest. We opted for an unequal allocation ratio as it has been supported as an alternative approach for ‘confirmatory trials’ [68, 69], primarily to increase the amount of data on the INT, where individual responses are likely more variable. We presume limited variability in the CON group, as participants will continue to live their normal lifestyle. Any small loss of precision with the use of unequal allocation has been appropriately accounted for in the sample size calculation. While participants may have a strong preference to receive the INT and not be in the CON group, we will try to overcome this by offering a waiting-list control. Participants in the CON group will, therefore, be offered the opportunity to participate in the INT once they have completed the CON period.

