#### Power calculation and sample size

The sample size was calculated using statistical software (G*Power 3.1.5) on the main outcome measure, fasting serum insulin concentration. This calculation was based on data from a hand-cycling training group, which reported an improvement of −14.3 ± 12.7 pmol l^−1^ [59] in fasting insulin over 16 weeks. Based upon these data (Cohen’s *d* = −1.1) it was estimated that nine participants are required to detect a statistically significant change in insulin sensitivity in the INT group. The power was 0.8 and the alpha was set at 0.05. As a 2:1 ratio is to be adopted, a computer programme (www.statstodo.com/SSizUnequal_Pgm.php) was used to calculate sample size adjustments for two groups with unequal size, to account for any consequences of unequal allocation on statistical power [99]. Also, taking into account an expected drop-out rate of approximately 15 %, we aim to recruit at least 24 (INT: 16, CON: 8) participants with chronic paraplegia.

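### The group × day ANOVA is a valid change-score comparison, but for outcomes measured once per visit it gives up precision that baseline-adjusted ANCOVA would recover, unless the baseline/follow-up correlation is near 0.9

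*Protocol article*

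**What the plan says.** Under Statistical analysis, the article states that "Changes in key outcome variables within and between trials will be analysed with two-way (group [INT, CON] × day [baseline, follow-up"]) mixed-model ANOVA, with a three-way version that adds time. No baseline covariate is named. If an interaction is significant, t tests follow, "both between treatments at each time point and between time points within each treatment relative to baseline". On multiplicity it adds: "Both methods will be subjected to a Holm-Bonferroni stepwise adjustment".

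Under Recruitment and randomisation, the first nine participants are allocated from a 2:1 block. Later participants are allocated by "minimisation [67] to ensure balance between the two groups for baseline characteristics (age, body mass, level of spinal cord lesion and physical activity level"). The baseline value of the outcome is not among these factors.

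Under Power calculation and sample size, the calculation is based "on the main outcome measure, fasting serum insulin concentration". It uses a training group "which reported an improvement of −14.3 ± 12.7 pmol l^−1", taken as d = −1.1. The recruitment target is 24 (16 INT, 8 CON), with about 15% dropout expected.

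**The concern.** With one baseline and one follow-up value, the interaction in a group × day ANOVA uses baseline only by subtraction. Subtraction is the best use of baseline only when the regression of follow-up on baseline has slope 1. At a lower correlation it over-corrects: the estimate is noisier than it need be, and part of any chance baseline difference carries through to the result. In a trial of 24 people allocated 2:1, with the sizing outcome left out of the minimisation, such differences can be sizeable.

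The follow-up t tests also direct attention to contrasts that do not estimate the treatment effect. One compares the groups at baseline, where a difference reflects chance. The others are separate pre–post tests within each arm. The stake is precision and clear interpretation in a very small trial.

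**Working it through.** **1. Inputs.** From the article: mean change −14.3 and SD 12.7 pmol/l, d = 1.1 in absolute value (14.3/12.7 = 1.126), alpha 0.05, power 0.8, target 16:8, dropout about 15%. Assumed: two-sided test, the same SD of change in both arms, no change in CON, equal variance at the two visits, and a baseline/follow-up correlation r from 0.3 to 0.9. The article gives no r.

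**2. The article's own figure.** A paired t test, two-sided 0.05, d = 1.1, has power 0.82 at n = 9 (0.76 at n = 8), so nine reproduces. Treating nine as a per-arm number and converting to 2:1 gives 6.75 + 13.5 = 20.25. Then 20.25/0.85 = 23.8, so 24. The nine describes a change within INT, not the between-group contrast that the ANOVA tests.

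**3. Equivalence.** With two days, the interaction F equals the square of the two-sample t on change scores. A numerical check gave 0.0609 for both.

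**4. Power of the planned test at 16:8.** Standard error factor √(1/16 + 1/8) = 0.433. Noncentrality 1.1/0.433 = 2.540 on 22 df. Power = 0.68.

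**5. ANCOVA at 16:8.** In large samples, Var(ANCOVA)/Var(change) = (1 − r²)/[2(1 − r)] = (1 + r)/2. Estimating the slope multiplies this by (N − 3)/(N − 4) = 21/20 = 1.05. Noncentrality is 2.540/√ratio on 21 df.

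| r | (1 + r)/2 | finite-sample ratio | noncentrality | power, ANCOVA | power, planned |
|---|---|---|---|---|---|
| 0.3 | 0.65 | 0.68 | 3.08 | 0.83 | 0.68 |
| 0.5 | 0.75 | 0.79 | 2.86 | 0.78 | 0.68 |
| 0.7 | 0.85 | 0.89 | 2.69 | 0.73 | 0.68 |
| 0.8 | 0.90 | 0.95 | 2.61 | 0.70 | 0.68 |
| 0.9 | 0.95 | 1.00 | 2.54 | 0.68 | 0.68 |

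Simulation at 16:8 agreed to within about 0.01, and both tests had type I error of about 5%.

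**6. After dropout.** 24 × 0.85 is about 20, taken as 13:7. The planned test has power 0.60. ANCOVA has 0.76, 0.70, 0.64, 0.62 and 0.60 over the same values of r.

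**7. Chance imbalance.** If baseline insulin is unrelated to the minimisation factors, the standard error of its between-group difference at 16:8 is √(1/16 + 1/8) = 0.43 SD. Given an imbalance, the change-score estimate is shifted by (1 − r) times it, in the opposite direction. At r = 0.5, an imbalance of 0.43 SD shifts the estimate by about 0.22 SD. ANCOVA removes this shift.

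**The case against.** The strongest reply is that the planned analysis is a legitimate between-group test and that this is only a preference about efficiency. Much of that stands. Several stronger readings are tempting, and the article does not support them.

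- **That the ANOVA ignores baseline or is biased by regression to the mean.** It uses baseline by subtraction. Under randomised allocation, expected regression to the mean is the same in both arms, so the estimate is unbiased. What remains is inefficiency, and sensitivity to whatever imbalance occurs.
- **That the within-arm tests let a benefit be claimed without the control group.** The t tests run only after a significant interaction, which is itself the comparison with control, and they are Holm-adjusted. With no true group difference, that gate opens about 5% of the time per outcome. The within-arm tests remain uninformative about the treatment effect, but they do not bypass the control group.
- **That the follow-up tests always include a baseline-visit comparison.** Under Blood sampling and Oral glucose tolerance test, baseline also means the fasting sample before glucose, so the wording may mean something else in the three-way model. In the two-way model the only time points are the two visits, and there the reading is fair.
- **That the gain costs nothing or is assured.** ANCOVA costs one degree of freedom, the (1 + r)/2 ratios overstate the gain at this size, and near r = 0.9 there is none.
- **That leaving the minimisation factors out of the model is an error.** A covariate list can sit in a fuller plan that is not shown. With about 21 completers, four uninformative covariates could cost about 0.12 in power.

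The article also expects less variability in CON than in INT, so the equal-SD assumption is a simplification and the absolute power figures would shift without it.

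**Conclusion.** The point holds as one of efficiency, not validity. The article fixes a change-score comparison for single-value outcomes where a more precise analysis of the same data is available. Under the stated assumptions the power gain at 16:8 is about 15 points at r = 0.3, 10 at 0.5, 5 at 0.7, 2 at 0.8 and none at 0.9. Since r is not given, the gain can only be stated as that range. It matters more because, on these assumptions, the planned contrast has 0.68 power against the 0.8 cited in the sizing. Only at r = 0.3 in the table does ANCOVA reach 0.8, so it is not a remedy for the sample size. The baseline-visit test and the within-arm tests add nothing to the estimate of effect, even though they are gated and adjusted.

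**What to change.** For each outcome with one value per visit, including summary measures such as iAUC, make the primary analysis an ANCOVA of the follow-up value on group with the baseline value as covariate. Report the adjusted INT–CON difference with its 95% CI. Drop the between-group test at the baseline visit and show within-group changes descriptively. A supporting model with the four minimisation factors is optional.

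The cost is a change of analysis wording and one degree of freedom, with little or no gain if r is near 0.9. No extra participants or measurements are needed. Under Blood measurements, all variables except the haematological profile are assayed in one batch after the last participant finishes, so for insulin the change can be fixed before results exist.

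### Magnitude-based inference is planned on every variable with no stated error control and no rule of precedence, so it can label as beneficial an outcome that the planned test does not support

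*Protocol article*

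**What the plan says.** All of this is in one paragraph, the Statistical analysis section of the protocol article. The main analysis is a mixed-model ANOVA, "two-way (group [INT, CON] × day [baseline, follow-up]) and three-way". Post hoc testing depends on its result: "Where significant interactions are observed, multiple *t* tests will determine the location of variance". Those t tests compare the groups at each time point, and time points within each group. The next sentence reads "Both methods will be subjected to a Holm-Bonferroni stepwise adjustment".

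Cohen's d is then promised for all variables, with the remark that "thresholds of >0.2 (small), >0.5 (moderate) and >0.8 (large) have been suggested". The paragraph closes with "Magnitude-based inferences will also be calculated to examine the impact of exercise on all variables of interest".

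The article gives no variant of magnitude-based inference, no smallest worthwhile effect, no probability cut-offs and no error rate. It does not say which result governs if the ANOVA and the magnitude-based label disagree.

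**The concern.** Magnitude-based inference takes the estimate and its standard error, treats them as a flat-prior posterior, and turns the chance that the effect exceeds a smallest worthwhile value into words such as 'possibly' or 'likely' beneficial. It uses no information beyond the estimate and its interval, but it can attach a positive label to a result well short of the 5% level.

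The article gives it an inferential purpose (the impact of exercise) and applies it to every variable. It needs neither a significant interaction nor the Holm step. The trial is small, has many outcomes, and is meant to help inform physical activity guidelines (Discussion). Positive labels that the planned test does not back could therefore enter the evidence on which such guidelines are built.

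**Working it through.** **The plan's own figures.** Power calculation and sample size gives a change in fasting insulin of −14.3 ± 12.7 pmol/l, d = −1.1, power 0.8 and alpha 0.05. A paired t test at two-sided 5% with d = 1.1 has power 0.76 with 8 participants and 0.82 with 9, so nine reproduces. For 2:1 allocation at the precision of 9 per arm, 1/9 + 1/9 = 1.5/c gives c = 6.75 controls and 13.5 intervention, 20.25 in all. Then 20.25/0.85 = 23.8, or 24 (16:8). Expected completers are 16 × 0.85 = 13.6 and 8 × 0.85 = 6.8, taken as 14 and 7.

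**Assumptions, because the article gives none.** Flat prior; smallest worthwhile effect 0.2 between-subject SD (the article's 0.2 belongs to Cohen's d and is only borrowed here); true effect zero; pre-post correlation r, so that the SD of change is √(2(1 − r)), which equals 1 at r = 0.5.

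**Formulas.** Let D be the between-group difference in mean change (positive = benefit), s its standard error, and T the t distribution function on 14 + 7 − 2 = 19 df.
- Chance of benefit = 1 − T((0.2 − D)/s)
- Chance of harm = T((−0.2 − D)/s)

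With two days, the group × day interaction is the t test of D, so the two methods can be compared directly.

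**How large D must be at r = 0.5.** A typical s is √(1/14 + 1/7) = 0.463.
- 'Likely' (>75%): 0.2 + 0.688 × 0.463 = 0.52 SD
- 'Likely', and also under 5% chance of harm: −0.2 + 1.729 × 0.463 = 0.60 SD (the larger of the two conditions)
- Two-sided 5% test: 2.093 × 0.463 = 0.97 SD

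A difference between about 0.5–0.6 and 0.97 SD is thus labelled 'likely beneficial' while the test is not significant.

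**Rate of false benefit labels** (simulation of null trials, 14:7, s allowed to vary, benefit direction only):

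| r | >75% | >75% and harm <5% | 'Possibly': >25%, and benefit and harm not both >5% | >25% and harm <0.5% | >95% |
|---|---|---|---|---|---|
| 0 | 16% | 9% | 9% | 1.1% | 2.6% |
| 0.5 | 13% | 11% | 11% | 1.5% | 2.0% |
| 0.7 | 11% | 11% | 13% | 2.0% | 1.5% |
| 0.8 | 9% | 9% | 16% | 2.6% | 1.1% |
| 0.9 | 5% | 5% | 23% | 4.5% | 0.5% |
| 0.95 | 2% | 2% | 23% | 8.7% | 0.2% |

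The two-sided 5% test gives 2.5% in every row. At 16:8 the pattern is similar; the 'possibly' column peaks at about 25% (r = 0.9).

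At r = 0.5, counting benefit or harm doubles the first two columns to 27% and 21%. About three quarters of the false labels in the second column have p > 0.05 there.

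**Over the main outcomes.** Table 1 and the Blood measurements text give 11 biochemical, adipokine and inflammation markers, two incremental areas under the curve, the Matsuda index and three HOMA-2 estimates: 11 + 2 + 1 + 3 = 17. Expected false 'likely beneficial' labels at r = 0.5, if every effect were zero: 17 × 0.106 = 1.8 to 17 × 0.134 = 2.3. From the test: 17 × 0.025 = 0.4.

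**The case against.** Four points can be made for the plan.

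*The numbers are not the document's.* Correct: rule, smallest effect and correlation are all assumed, and strict rules do no worse than the test. Above all, a reader might infer that a fifth to a quarter of null effects would be called benefits. In the central scenario, 21 to 27% counts labels of benefit and harm together; benefit alone is about half that. A benefit rate of a fifth to a quarter needs the 'possibly' rule and, between groups, a high correlation.

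*Holm is not undone.* Also correct. A reader might infer that the magnitude-based labels cancel a correction across outcomes. On its natural reading, the Holm sentence covers the two sets of post hoc t tests after a significant interaction, and no adjustment across variables is described. The ANOVAs are then themselves unadjusted over the many outcomes. What stands is narrower: the labels bypass the interaction test and the post hoc adjustment.

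*The article does not say that the labels will decide anything.* It says only that they will also be calculated. A reader might infer a declared second route to an efficacy claim, and the text does not go that far. But it gives the method an inferential purpose, does not confine it to description and sets no order of precedence.

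*Cut-offs may be left to a fuller plan.* They may, and their absence is not the point. The point is the stated choice to apply this method to every variable with no limit on its role.

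**Conclusion.** The point holds in this form: the article plans magnitude-based inference as an inferential method on all variables, with no stated error control and no rule on whether it or the ANOVA governs. It can therefore call beneficial an outcome that the planned test does not support.

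The size is conditional. In the central scenario above, the false 'likely beneficial' rate is roughly four to five times that of the test. Across the rules and correlations examined, it extends from below 1% (>95% rule at high correlation) to about 25% ('possibly' rule at high correlation). It exceeds 2.5% in most scenarios, but not under every rule.

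**What to change.** Replace the magnitude-based inference sentence with two statements. First, for every variable the between-group difference in change is reported with its 95% CI, and its size is discussed against that interval. Second, claims of effect rest only on the pre-specified group-by-day test.

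This alters wording and removes one analysis; no data collection changes. The loss is the verbal magnitude labels, and Cohen's d is already planned for all variables to convey effect size. Keeping the labels as description only, with the ANOVA stated to govern, would settle precedence, but would leave wording that reads as evidence beside non-significant tests. Replacement is cleaner. According to Blood measurements, all assays except the haematological profile are run in one batch after the last participant finishes, so the change can be fixed before those results exist.
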